**Figure 1 f1:**
[figure not shown]
Schematic overview of study design. ALK, Anaplastic lymphoma kinase; BID, twice daily; C_min,SS_, minimum plasma concentration during steady state; ctDNA, circulating tumor DNA; mPFS, median progression free survival; mOS, median overall survival; ORR, overall response rate; R, Randomization; TDM, Therapeutic Drug Monitoring.

Patients who start alectinib treatment at the approved European standard dose of 600 mg BID will be screened and if eligible, randomized into arm A or B. First PK samples will be collected at 4 weeks after start of treatment. Subsequently, plasma samples will be drawn to evaluate the plasma trough concentration every 8 weeks in the first year of treatment, then every 12 weeks thereafter. Blood collection and analysis will be combined with regular safety lab measurements during standard routine visits, therefore causing limited additional burden for the patients. The flowchart consisting of the schedule of assessments can be found in **Supplemental Table 1**.

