#### Intervention and control group

2.2.1

For patients in arm A (TDM group) plasma trough concentrations of alectinib will be analyzed directly from the PK samples. Results will be available within 1-2 weeks. In case of C_min,SS_ below the threshold of 435 ng/mL (in arm A) and no or limited toxicity, the patient receives a dose increase with 150 mg BID to a maximum of 900 mg BID. The dose levels are shown in **Table 1**. Four weeks after a dose increase, an extra PK sample is drawn to check whether the intervention was successful, i.e. when TDM target is reached with acceptable tolerability. When patients have adequate exposure (C_min,SS_ ≥ 435 ng/mL), the dose will be continued given no or acceptable toxicity. For patients in arm B, PK samples will be drawn conform the same schedule as patients in arm A. However, these samples will remain blinded to the patients and the treating physician until the end of the study. In case of unmanageable toxicity in both arms (i.e. unbearable or persistent grade 2 toxicity, or grade 3/4 toxicity according to Common Terminology Criteria for Adverse Events (CTCAE) v5.0), the alectinib dose can be reduced by one dose level (150 mg BID) in accordance with standard care unto a minimum of 300 mg BID. Temporary dose interruptions are allowed. If the side effects subside or are no longer present, it is allowed to increase the dose again. To estimate the C_min,SS_ of alectinib, the time of blood draw will be recorded and all patients will keep a paper diary to collect date and time of last intake of alectinib. Alectinib C_min,SS_ will be calculated with the following formula:

**Table 1 T1:** dose levels of alectinib.

Dose level	Alectinib Dose
-2	300 mg BID
-1	450 mg BID
0	600 mg BID
+1	750 mg BID
+2	900 mg BID

$$C_{min,SS}=\;C_{measured}*0.5^{\frac{dosing\;interval-TAD}{t_{1/2}}}$$

Where C_min,SS_ is the estimated minimum plasma concentration, C_measured_ the measured plasma concentration, the dosing interval is the time between two subsequent administrations, TAD is time after dose and t_1/2_ is the elimination half-life of the drug (i.e. 32 hours for alectinib). PK samples should be drawn after at least 4 hours after the last intake of alectinib (after T_max_) (16). It is assumed that this algorithm should perform equivalently, and most likely even better, as imatinib validated by Wang et al, since the half-life of alectinib is longer (16).

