#### Sample size calculation

2.3.2

It is expected that 48% of the patients treated with alectinib in our study will be underdosed (i.e. C_min_ < 435 ng/mL at a certain timepoint) based on the dataset of Groenland et al. (13). The observed mPFS for these patients was 12.6 months (95% confidence interval (CI): 9.2 months – not yet reached), which will serve as the assumed median in the subgroup with low exposure in the fixed-dosing group (arm B). The mPFS in the patients with C_min_ ≥ 435 ng/mL had not yet been reached (95% CI: 19.8 months – not yet reached) at the time of analysis, but the HR for the group with C_min_ < 435 ng/mL versus C_min_ ≥ 435 ng/mL was estimated as 2.5 (13). We expect that TDM-guided dosing can improve PFS in 67% of patients with a low exposure, to the extent that they obtain a similar outcome as patients with C_min_ ≥ 435 ng/mL. In this group, a HR (fixed versus TDM-guided dosing) of 2.5 is assumed. In the remaining 33% of patients, TDM-guided dose increases are expected not to be feasible due to toxicity or treatment discontinuation as a consequence of progressive disease (PD), so a HR equal to one is assumed for this subgroup. Altogether, this would result in an expected HR (fixed versus TDM-guided) of 2.0. With 67 events, a power of 80% will be obtained to detect this HR of 2 using the log-rank test and assuming a two-sided significance level of 5%. This translates into an improvement in mPFS from 12.6 months without using TDM-guided dosing to 25.2 months using TDM-guided dosing. Assuming an uniform patient accrual during 48 months and 12 months follow-up after inclusion of the last patient (total study duration of 60 months), 94 patients (47 per group) with C_min _< 435 ng/mL will need to be included for the primary analysis. Since 48% of the patients in the study are expected to have C_min _< 435 ng/mL at a certain timepoint, 196 patients will need to be recruited (13). Dropouts are expected to be kept to a minimum and it does occur, it is expected to be in the first 12 weeks, when substitution is still allowed. Dropouts are therefore not taken into account.

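### The 80% power and the 25.2-month arm A median assume HR 2.0 from the start of treatment, but the dosing schedule keeps both arms on the same dose for at least 5 to 6 weeks

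*Protocol article*

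**What the plan says.** All places are in the protocol article.

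- **Section 2.3.2, Sample size calculation.** "We expect that TDM-guided dosing can improve PFS in 67% of patients with a low exposure", and in these patients a HR (fixed versus TDM-guided) of 2.5 is assumed. The other 33%, in whom an increase is not feasible because of toxicity or discontinuation for progression, are given HR 1. "Altogether, this would result in an expected HR (fixed versus TDM-guided) of 2.0". Then: "With 67 events, a power of 80% will be obtained to detect this HR of 2 using the log-rank test", two-sided at 5%, and "This translates into an improvement in mPFS from 12.6 months without using TDM-guided dosing to 25.2 months using TDM-guided dosing". Accrual is uniform over 48 months with 12 months of further follow-up. 94 low-exposure patients are needed, hence 196 recruited.
- **Abstract (Methods) and section 2.2, Study design.** Both arms start on the same fixed dose. "First PK samples will be collected at 4 weeks after start of treatment"; later samples follow every 8 weeks in the first year.
- **Section 2.2.1, Intervention and control group.** "Results will be available within 1-2 weeks". In arm A the dose rises one level at a time, with at most two levels above the starting dose. "Four weeks after a dose increase, an extra PK sample is drawn to check whether the intervention was successful".
- **Section 2.3.3, Primary outcome.** PFS counts from the start of treatment, in the subgroup with a low trough concentration.

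**The concern.** A single HR of 2.0 and an exact doubling of the median describe two arms whose hazards differ by a constant factor from the first day. The design cannot produce that. Until the first low result has been acted on, an arm A patient with low exposure is treated exactly like an arm B patient. Follow-up during that time adds events to both arms at the same rate and dilutes the log-rank comparison.

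The 33% with HR 1 do not represent this delay. They are patients in whom an increase never becomes feasible. The 67% who do benefit also wait for their result, and the calculation allows them no waiting time.

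Two stated figures are at stake: the power, and the arm A median against which the result will be read. A null result would be judged against 80% power that the design does not have.

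**Working it through.** **1. Reproduce the plan's figures (no lag).**

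- Events (Schoenfeld, 1:1): 4 × (1.960 + 0.842)² / (ln 2)² = 65.3, so 66. At 67 events: √67/2 × 0.693 − 1.960 = 0.877, giving 81.0% power.
- Event probability with uniform accrual over 48 months and analysis at month 60: 1 − [exp(−12λ) − exp(−60λ)] / (48λ). With λ = ln 2/12.6 this is 0.818; with λ = ln 2/25.2 it is 0.601. Expected events: 47 × (0.818 + 0.601) = 66.7.
- Recruitment: 94/0.48 = 195.8, so 196.
- Simulated log-rank power, 47 per arm, 20,000 runs: 79.9%.

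The arithmetic is sound, and it holds for hazards that separate at time 0.

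**2. Lags that follow from the schedule.**

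- One step: week 4 + 1-2 weeks for the result = week 5-6.
- Two steps: a further 4 weeks to the check sample + 1-2 weeks for its result = week 10-12.

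These apply to a patient who is low at the first sample. A patient first found low at a later sample changes dose later still.

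**3. Power with the lag.** Arm A has the arm B hazard (ln 2/12.6 per month) until the dose change and half of it afterwards; 47 per arm, analysis at month 60, two-sided 5% log-rank test. No subgroup event is allowed before week 4, because membership needs a measured low value. The share needing two steps is not in the document; 30-60% is an assumption. Each range runs from the longer lags (weeks 6/12) to the shorter (weeks 5/10).

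| Share needing two steps | HR 2.0 after the lag | Lag-period progression credited to the 33% |
|---|---|---|
| None | 77-78% | 78-79% |
| 30% | 73-76% | 77-78% |
| 60% | 72-74% | 76-77% |

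Separate simulations of these cases agree to within a point or so. Taken together they span 71-77% for a 30-60% two-step share, and about 76-79% with the credit. Expected events stay at about 66, so the loss does not come from fewer events.

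**4. How the credit works.** Suppose everyone who progresses during the lag belongs to the 33%. The share benefiting among those still progression-free is then q = 0.67/s, where s is the proportion who get through the lag. With the plan's own averaging, post-lag HR = 2.5q + (1 − q). Example, one step at week 6: the lag beyond week 4 is 2 weeks = 0.46 months, s = exp(−0.0550 × 0.46) = 0.975, q = 0.687, HR = 2.03, power about 78%.

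**5. Arm A median.** With the control hazard from day 0 and HR 2.0 after a lag of L months, solve 0.5^(L/12.6) × 0.5^((t − L)/25.2) = 0.5. This gives t = 25.2 − L.

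- 5 weeks = 1.15 months: 24.1 months
- 6 weeks = 1.38 months: 23.8 months
- 12 weeks = 2.76 months: 22.4 months

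The median uses a day-0 hazard so that arm B keeps its stated 12.6 months; the powers in step 3 use the week-4 condition. A restated calculation should use one convention for both.

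**The case against.** **HR 2.0 may be a net effect over follow-up.** Section 2.3.2 speaks of patients obtaining an outcome similar to that of adequately exposed patients. If 2.0 were already an average including the waiting time, imposing HR 1 first would discount it twice. But the section does not say so. It builds 2.0 from two subgroups without reference to time (0.67 × 2.5 + 0.33 × 1 = 2.005) and converts it to an exact doubling of the median, which is a constant-hazard step.

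**The 33% already cover early progression.** This stands in part, since discontinuation for progression is one of the reasons given. Crediting all lag-period progression to that group recovers some of the loss, but power stays at 76-79%.

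**The loss depends on assumptions.** This stands for the size. The one-step/two-step split is not given, and the simulation allows no benefit from a first step in patients who need two, which is the extreme case. Allowing a partial first-step effect (HR √2 between steps, also an assumption) together with the credit brings power to 77.9-79.7%.

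**The Discussion already calls HR 2.0 somewhat challenging**, and section 3 foresees talks with the DSMB about patient numbers and follow-up. Neither mentions the delay or revises the power.

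Two stronger readings are tempting, and the document does not support them:

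- *That the sample size arithmetic is wrong.* It reproduces; the fault lies in the model behind it.
- *That power is only in the 60s.* Applying full hazard from day 0 gives 65-73% for a two-step share of 0-60%. But the subgroup needs a measured low value, and a patient who progresses and stops before week 4 generally cannot supply one. Oligoprogression with continued alectinib is the exception. That range is a lower case, not the main estimate.

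**Conclusion.** Wrong as written, of modest size. The 80% power and the 25.2-month arm A median rest on a constant-HR model without lag, which the protocol's own sampling and dose-step schedule contradicts. Given the plan's other inputs, the direction is not in doubt; power fell below the stated 80% in every lag scenario examined. Under the week-4 condition the shortfall is usually about 1 to 9 points: about 77-78% with one step for all, 71-77% with 30-60% needing two, and 76-79% with lag-period progression credited to the 33%.

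These figures assume a post-lag HR of 2.0 (or its credited equivalent), full effect as soon as the final dose step is taken, and a first low value at week 4. They also keep the plan's way of averaging the 67% and 33% groups, which is a separate question. The median of about 22.4 to 24.1 months further assumes that the control hazard runs from day 0.

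**What to change.** In section 2.3.2:

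- Redo the calculation with HR 1 up to the expected time of the dose change, taken from sections 2.2 and 2.2.1, and the assumed HR afterwards.
- State the assumed one-step/two-step split, and how events before the first sample and progression during the lag are handled.
- Restate the power at 67 events (in the 70s rather than 80%) and the expected arm A median in place of 25.2 months.
- If 2.0 was meant as an average over follow-up, say so and justify it on that basis.

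The log-rank test, the number of patients and the schedule do not change. The cost is one recalculation, a sentence or two of text, and a stated power that is a few points less favourable. The DSMB would also have a sounder basis for the discussions on accrual and follow-up that the protocol foresees.

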#### Primary outcome

2.3.3

The primary outcome, based on our aim to improve efficacy of alectinib treatment, is mPFS in the TDM-guided dosing arm for the C_min,SS _< 435 ng/mL subgroup, compared to this subgroup in the fixed dosing arm (standard care). PFS will be calculated as time from start of treatment to PD, death of any cause, whichever occurs first. Patients who do not progress, die, or are lost to follow-up, will be censored at their last available date. PD is defined according RECIST v1.1 and will be based on assessment using CT scans (thorax/abdomen) and MRI of the brain. In case of oligoprogression alectinib may be continued conform standard of care, but the date of oligoprogression (i.e. PD) will be used in PFS calculation. The CT scans will be performed every 8 weeks in the 1^st^ year and every 12 weeks from the 2^nd^ year onwards. The MRI of the brain will be performed every 16 weeks in the 1^st^ year if there is presence of asymptomatic brain metastases at screening and every 24 weeks from the 2^nd^ year onwards. If no brain metastases are found at screening, an MRI of the brain will be performed every 12 months (**Supplemental Table 1**).

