### Aim and objectives

2.1

The aim of this RCT is to investigate the effect of TDM-guided dosing of alectinib on treatment outcomes of patients with ALK+ NSCLC. We hypothesize that using TDM to increase the dose of alectinib in patients with C_min,SS_ < 435 ng/mL if tolerable, will raise the mPFS. The primary objective will be to demonstrate, among patients who had a C_min,SS_ < 435 ng/mL at any time point during treatment, a prolonged mPFS in the TDM-guided dosing arm compared to the fixed dosing arm. Feasibility and tolerability of TDM, patient and physician adherence, overall response rate (ORR), median overall survival (mOS), intracranial PFS, quality of life (QoL), toxicity, alectinib-M4 concentrations and cost-effectiveness of TDM will be evaluated as secondary objectives. In addition, exploratory data will be collected on circulating tumor DNA (ctDNA) and its association with response and types of resistance to therapy. Data regarding the influence of alectinib on body composition will also be collected as exploratory objective, as weight gain is a known but not well understood side-effect.

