### Study design

2.2

The ADAPT ALEC trial is an international, multicenter, phase IV, RCT comparing TDM-guided dosing to standard dosing of alectinib. Initially the trial will be open at seven study sites in the Netherlands, after which international sites will follow. The study design is displayed in **Figure 1**. Patients will be centrally randomized according to the minimization method in a 1:1 ratio, stratified by prior treatment with other ALK inhibitors and presence of brain metastases, using the online randomization tool ALEA v.18.3 (FormsVision BV, Abcoude, The Netherlands). The trial will compare, in the subgroup of patients with alectinib plasma concentration C_min,SS_ < 435 ng/mL at any time point, those receiving dose-adjusted alectinib based on TDM (arm A) with those receiving standard treatment with fixed dose alectinib (arm B).

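### The primary subgroup is defined after treatment start and without a pre-progression limit, while PFS runs from treatment start: both medians come out too long and the contrast is slightly diluted

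*Protocol article*

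**What the plan says.** All references are to the protocol article.

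- **Time origin** (Primary outcome): "PFS will be calculated as time from start of treatment to PD, death of any cause, whichever occurs first".
- **Population** (Aim and objectives): the primary objective is to be shown "among patients who had a C_min,SS_ < 435 ng/mL at any time point during treatment". Study design repeats the rule: the comparison is made "in the subgroup of patients with alectinib plasma concentration C_min,SS_ < 435 ng/mL at any time point".
- **When membership can be established** (text after Figure 1): "First PK samples will be collected at 4 weeks after start of treatment". Sampling then continues "every 8 weeks in the first year of treatment, then every 12 weeks thereafter".
- **When TDM can act** (Intervention and control group): a dose increase follows a low result in arm A only, and "Results will be available within 1-2 weeks". Both arms are sampled on the same schedule; arm B results stay blinded.
- **Treatment after progression** (Primary outcome): "In case of oligoprogression alectinib may be continued conform standard of care", while the date of oligoprogression is the PFS event.
- **Analysis** (Data analysis): stratified log-rank test, stratified Cox model, Kaplan-Meier medians. No landmark, delayed entry or later time origin is described.

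**The concern.** Membership of the primary subgroup is decided after time zero. Two separate things follow.

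1. **Qualification before progression.** The interval from treatment start to the first low sample is event-free by construction. During it neither arm has a TDM dose increase, so it adds equal, uninformative time to both arms and lengthens both medians. Patients who stay on treatment longer give more samples and have more chances to qualify.
2. **Qualification after progression.** Such a patient brings a PFS event that came before any TDM action was possible. This adds no guaranteed time. It adds events without a treatment contrast.

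The article names median PFS as the primary outcome, so the headline quantity itself is affected. Both the time origin and the membership rule are fixed in the article, so an analysis plan that follows them inherits the problem.

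**Working it through.** **Step 1. The plan's own figures** (Sample size calculation: HR 2.0, two-sided 5%, medians 12.6 and 25.2 months, accrual 48 + follow-up 12 months, 48% low).

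- Schoenfeld: 4 × (1.96 + 0.8416)² / (ln 2)² = 65.3, so 66 events. With 67 events, √67/2 × ln 2 − 1.96 = 0.877, which is power 81.0%.
- Event probability with hazard λ = ln 2/median: 1 − (e^(−12λ) − e^(−60λ))/(48λ), giving 0.818 and 0.601. Then 47 × (0.818 + 0.601) = 66.7, so 67 events.
- 94/0.48 = 195.8, so 196.

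The design reproduces with a constant hazard from time zero, that is, with no guaranteed time.

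**Step 2. Smallest possible effect.** If every member qualifies at week 4 (4 × 12/52.18 = 0.92 months), exponential hazards give medians from treatment start of 0.92 + 12.6 = 13.5 and 0.92 + 25.2 = 26.1 months.

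**Step 3. Later qualification.** The article does not give the time to first low sample, so the week-4 share is varied. Assumptions: stated PK schedule; late qualifiers turn low at 15% per sample; arm A hazard halves at the first low sample; all qualify before progression; 47 per arm.

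| Low at week 4 | Median B / A, months | HR | Events | Power, plan's clock | Power, clock from first low sample |
|---|---|---|---|---|---|
| 100% | 13.5 / 26.1 | 1.99 | 66 | 80% | 80% |
| 80% | 14.5 / 27.3 | 2.00 | 65 | 77% | 79% |
| 60% | 15.8 / 28.6 | 1.97 | 63 | 75% | 77% |
| 40% | 17.4 / 30.3 | 1.95 | 61 | 72% | 75% |

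Counted from the first low sample, medians return to about 12.6 and 25.2 and the HR to about 2.0. The ratio of medians falls from 2.0 to between 26.1/13.5 = 1.93 and 30.3/17.4 = 1.74. With no treatment effect, simulated type I error was 5.3%.

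**Step 4. How late is qualification likely to be?** Model: typical trough log-normal, median 517 ng/mL and CV 57% (Introduction); hazard from 12.6 months if typically low, divided by 2.5 otherwise; within-patient CV assumed, because the article gives none. Arm B medians:

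| Within-patient CV | First low after week 4 | Plan's clock | From first low, or delayed entry | Difference |
|---|---|---|---|---|
| 10% | 22% | 17.2 | 15.0-15.3 | 1.9-2.2 |
| 12% | about 25% | 18.2 | 15.6-15.7 | 2.5-2.6 |
| 20% | 35% | 20.4 | 17.1 | 3.3 |

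Repeat runs differ by a few tenths of a month. A CV of about 12% reproduces the stated 48% ever low; a CV of 20% gives about 55% and fits less well. For arm A the corresponding medians are 26.0 against 23.2-23.7 at 10% (difference 2.3-2.8) and 28.7 against 24.8-25.0 at 20% (difference 3.7-3.9).

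**Step 5. Qualification after progression.** If 30% continue for 6 months beyond progression (assumed, CV 20%), about 2.3% of the subgroup qualifies only then: 0.023 × 94, about 2 patients. In the Step 3 model, a 5% share (80% of the rest at week 4) gives HR 1.93 and power 73%. A 10% share gives HR 1.83-1.86 and power 67-71%. Moving the clock alone does not cure this: at 10%, HR is still 1.85-1.87 and power 69-71%.

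**The case against.** The strongest reply is that the test is sound and the harm small. Until the first low sample both arms follow the same dosing plan and sampling schedule, so the extra time falls equally on both. The clock costs at most about 3 points of power. This stands, and it limits the severity.

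A reader might infer three stronger things that the documents do not support:

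- **That the rule favours one arm.** Nothing stated makes qualification differ between arms before the first low result. Arm A physicians do see results after the week-4 sample, which is a reason for a week-4 sensitivity analysis but not evidence of bias.
- **That the clock explains the whole gap from 12.6 months, or ruins the power.** At a CV of 12%, 18.2 − 12.6 = 5.6 months, of which 3.0-3.1 remain after the correction. In the Step 4 model 23% (CV 10%) to 37% (CV 20%) of the subgroup are typically adequate patients who enter on a single low sample. Among typically low patients at a CV of 10%, the medians are 13.7 and 12.6, so the clock adds about 1 month. Power in that model is 0.36 and 0.275 at CVs of 10% and 20%, and only 0.38 and 0.294 with the clock moved. That loss belongs to the subgroup definition.
- **That the medians cannot be compared with 12.6 and 25.2 months.** The source patients were also classed as low at some point, and the source's time origin is not shown. The 12.6 months may already contain similar guaranteed time.

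It is also fair to say that sampling after progression is inferred from the words "among patients who had a C_min,SS_ < 435 ng/mL at any time point during treatment" together with continued treatment. The article does not state it outright, and the full assessment schedule is in a supplement not at hand.

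**Conclusion.** The point holds at moderate severity (should-fix). As written, the primary subgroup is formed after time zero with no requirement that the qualifying sample precede progression, and PFS is counted from treatment start.

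- **Medians:** too long by about 1 month if nearly all qualify at week 4. At assumed within-patient CVs of 10-20% the excess is about 2 to 3 months in arm B and up to nearly 4 in arm A at the upper end, which fits the stated 48% least well.
- **Hazard ratio and power:** small effect from the clock (1.95-2.00 instead of 2.0; 0 to 3 points), with expected events of 61-66 instead of 67.
- **Post-progression qualifiers:** a further dilution of unknown size, about 2% of the subgroup under the inputs of Step 5.
- **Validity of the comparison:** type I error is preserved.

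The direction follows from the article's text. The size depends on the share who qualify late, which the article does not give.

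**What to change.** 1. State that only a low sample taken before progression qualifies a patient for the primary subgroup.
2. Analyse PFS with delayed entry (left truncation) at the first low sample in both arms, or with that date as time zero. Choose one in advance. Keep PFS from treatment start as a description.
3. Add a sensitivity analysis in patients low at the week-4 sample, the only sample taken before any arm A result is known.
4. Treat the subgroup comparisons of OS (now from randomization) and intracranial PFS (now from treatment start) the same way.
5. Recheck the 67 events and 94 patients on this basis.

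**Cost:** no new data, because the time of blood draw is recorded and both arms are sampled alike. It is more than a wording change, since subgroup size and events may fall slightly. The medians will describe PFS conditional on, or counted from, the first low sample, which is a different quantity from PFS since treatment start. The change should be made before arm B levels are unblinded, so that it cannot look data-driven.
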